### 2.2 Sample size estimation and participants

We estimated that group sample sizes of 526 in each group will achieve 90.031% power to detect a difference between the group proportions of functional independence [modified Rankin scale (mRS) range from 0 to 2] at 90 days of 0.135. According to the Multicenter Randomized CLinical trial of Endovascular treatment for Acute ischemic stroke in the Netherlands (MR CLEAN) (14) trial, the proportion in control group is assumed to be 0.191 under the null hypothesis and 0.326 under the alternative hypothesis. The significance level of the test is 0.05. Considering a 20% dropout rate, the final sample sizes for both groups were 526. Given the large data requirements of machine learning, we doubled the sample size of each group based on the original estimates.

A total of 1,052 patients with acute large vessel occlusion stroke were enrolled from Ya'an People's Hospital, Ganzi Tibetan Autonomous Prefecture People's Hospital, and Liangshan Yi Autonomous Prefecture First People's Hospital (Figure 2), including both those who underwent endovascular treatment and those who did not. Although all patients met the current guideline-based indications for mechanical thrombectomy, some did not receive the procedure due to various factors, such as declining treatment over concerns about surgical risk or experiencing delays in transfer to thrombectomy-capable centers. In this study, these branch centers primarily served as referral sites or admitted patients who declined endovascular therapy. All participating centers implemented a standardized, homogeneous protocol for medical management. Prior to group assignment, patients who met the criteria for intravenous thrombolysis and had no contraindications were eligible to receive intravenous thrombolysis.

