### 2.4 Statistical analysis

Statistical analyses will be conducted using R version 4.3.3 by an independent statistician blinded to group assignments. Continuous variables will be tested for normality using the Shapiro–Wilk test (α = 0.05). Normally distributed data will be presented as means ± standard deviations and compared using the independent *t*-test or one-way analysis of variance. Non-normally distributed data will be presented as medians with interquartile ranges and compared using the Wilcoxon rank-sum test or Kruskal–Wallis test. Categorical variables will be summarized as counts and percentages, with group comparisons performed using the χ^2^ test or Fisher's exact test.

Given the non-randomized allocation of treatment (EVT vs. SMT), potential confounding by indication will be addressed using propensity score methods. A logistic regression model including baseline covariates (age, sex, baseline NIHSS, onset-to-enrollment time, comorbidities, and relevant imaging findings) will be used to estimate the propensity score for receiving EVT. We will perform both propensity score matching (1:1 nearest-neighbor without replacement, caliper = 0.2 SD of the logit) and inverse probability of treatment weighting (IPTW) to adjust for baseline imbalances. Standardized mean differences (SMDs) will be reported to assess covariate balance before and after adjustment.

Primary analyses will be performed on the matched cohort, with IPTW analyses conducted as sensitivity analyses. Logistic regression will be used for binary outcomes, linear regression for continuous outcomes, and ordinal logistic regression for ordinal outcomes, all adjusted for residual imbalances after matching. Results will be reported as adjusted odds ratios (aOR) with 95% confidence intervals (CIs).

To address missing data, multiple imputation using chained equations (MICE) will be employed under the missing-at-random assumption, generating 20 imputed datasets. Analyses will be conducted on each dataset, and results will be pooled using Rubin's rules. Sensitivity analyses will compare complete-case and imputed results to assess robustness.

All hypothesis tests will be two-sided, with *p* ≤ 0.05 considered statistically significant. No interim analyses are planned.

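### The stated power (90.031% at 526 per group) is for an unmatched comparison of whole groups, but the primary analysis uses only 1:1 caliper-matched pairs

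*Protocol article*

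**What the plan says.** Section 2.2 sizes the study on the primary outcome. It states that "group sample sizes of 526 in each group will achieve 90.031% power" for a difference in "functional independence [modified Rankin scale (mRS) range from 0 to 2] at 90 days of 0.135". It adds that "the proportion in control group is assumed to be 0.191 under the null hypothesis and 0.326 under the alternative hypothesis", which I read as 0.191 without and 0.326 with endovascular treatment. It also states: "The significance level of the test is 0.05". Section 2.4 adds: "All hypothesis tests will be two-sided".

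On the route to 526, section 2.2 says: "Considering a 20% dropout rate, the final sample sizes for both groups were 526". It then says that the groups were doubled to meet the data needs of machine learning. Nothing is set aside for patients who find no match.

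Section 2.4 specifies the matching as "1:1 nearest-neighbor without replacement, caliper = 0.2 SD of the logit" and says: "Primary analyses will be performed on the matched cohort, with IPTW analyses conducted as sensitivity analyses". Section 2.1 says that exposure is not assigned, so the equal split is a planning figure only.

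**The concern.** A sample-size statement should describe the analysis that will test the primary hypothesis. Here it describes a comparison of everyone enrolled, while the primary test is run on a subset whose size is unknown until the propensity scores are estimated.

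Matching without replacement loses little when there is a large reserve of untreated patients. With two planned groups of equal size there is no reserve: where the propensity distributions differ, the caliper leaves patients unmatched in both groups. Some separation is plausible. Section 2.4 itself expects confounding by indication, and section 2.2 gives transfer delay as a reason for non-treatment while onset-to-enrollment time is in the propensity model. If recruitment turns out unequal, the smaller group is the ceiling on pairs.

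At stake is whether readers, and the team monitoring accrual, know how many pairs the primary test needs. As written, 526 per group looks like the requirement and 90% looks like its consequence. Neither is so.

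**Working it through.** **Inputs.** p1 = 0.191, p2 = 0.326, difference d = 0.135, alpha 0.05, 526 per group, 20% dropout and the doubling (section 2.2); two-sided testing and a 0.2 SD caliper (section 2.4). The degree of propensity overlap is not given, so it is assumed below.

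**1. Reproducing the plan's figures.** Pooled two-proportion formula, with p̄ = 0.2585:

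n = [1.960 × √(2p̄(1 − p̄)) + 1.2816 × √(p1(1 − p1) + p2(1 − p2))]² / d²

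= [1.960 × 0.6192 + 1.2816 × 0.6118]² / 0.135² = 3.990 / 0.018225 = 218.9, so 219 per group.

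- 219 × 1.2 = 262.8, rounded up to 263; 263 × 2 = 526. This reproduces the group size.
- Power at 219 per group is 90.009% (pooled). The unpooled test gives exactly 90.031% at 216 per group. The stated percentage therefore belongs to a group of about 216 to 219.
- Power at 526 per group: Φ[(0.135 − 1.960 × 0.6192/√526) / (0.6118/√526)] = Φ(3.08) = 99.9%. So 90.031% is not the power at 526, even for the unmatched test.

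**2. What the matched analysis needs.** Treating the pairs as two groups of that size, 90% power needs about 219 pairs with an outcome.

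- With no dropout: 219/526 = 42% must match, so up to about 58% may go unmatched.
- After 20% loss: 526 × 0.8 = 421 per group, and 219/421 = 52% must match, so up to about 48% may go unmatched.

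**3. How many pairs might be available.** I simulated greedy 1:1 matching with a 0.2 SD caliper on normally distributed propensity logits, 421 per group, 100 runs per setting. The c-statistics are assumptions.

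| Assumed c-statistic | Share of 421 matched | Pairs | Power |
|---|---|---|---|
| 0.65 | 78% | about 329 | 98% |
| 0.75 | 63% | about 265 | 95% |
| 0.85 | 47% | about 197 | 87% |
| 0.90 | 37% | about 157 to 159 | 78% to 79% |

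At c = 0.60 about 85% match and power is above 98%.

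**4. Unequal split.** Take the same 842 evaluable patients split 590/252 (an illustration). The ceiling is 252 pairs, where power is 93.6% if every patient in the smaller group is matched. At c = 0.75 about 216 to 218 pairs form (power about 90%). At c = 0.85 about 167 to 170 form (about 81%).

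**The case against.** The strongest reply is that no harm has been shown. The doubling leaves the study well above the 219 per group that the formula needs, and power stays at or above 90% unless about 48% of evaluable patients go unmatched (58% without dropout). At c = 0.65 and 0.75 it is 98% and 95%. This stands. A reader might infer that the study is underpowered, but the documents do not support that.

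A reader might also infer that matching will discard some definite share, such as a quarter to 60%. The article gives no propensity distribution, and a loss of that size corresponds to c of roughly 0.67 to 0.88. Refusal of treatment, one of the stated reasons for non-treatment, is not among the listed propensity covariates, so separation could be weak. At c = 0.60 only about 15% would be lost.

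A third tempting step is to say that matching is the wrong primary method and that overlap weighting should replace it. Under these assumptions overlap weighting would carry about 15% to 40% more information. But the matched analysis is conventional and prespecified, with balance checks, adjustment for residual imbalance and a weighted sensitivity analysis. Overlap weighting also targets its own population. Reasonable statisticians differ on this choice, and nothing in the document makes matching an error.

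Finally, an expected matched fraction is detail that an article may leave to the full protocol. Its absence alone would not be a finding. The point rests on two things the article does state: a power figure tied to whole groups of 526, and a primary analysis confined to pairs.

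**Conclusion.** The power statement is wrong as written. It describes neither the primary analysis nor, at 526 per group, the unmatched test it appears to describe (99.9%, not 90.031%). The quantity that governs the primary test is the number of evaluable pairs, and 90% power needs about 219.

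Whether that number is reached depends on overlap and on the group split, neither of which the article gives. With equal groups and 20% loss, the doubled sample is ample under moderate separation (95% at c = 0.75), falls somewhat short at c = 0.85 (87%), and is clearly short at c = 0.90 (about 79%). If the true power turned out near 90%, that would be because about half of the evaluable patients happened to match.

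These figures assume normal logits, greedy matching, the stated event rates holding within the matched set, and pairs treated as two independent groups. They also assume that the 20% lost contribute nothing, in line with the exclusion of incomplete follow-up in section 2.1. If multiple imputation (section 2.4) keeps some of those patients, the position is better than shown.

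**What to change.** In section 2.2, state the requirement in the unit that is analysed: about 219 evaluable matched pairs for 90% power at 0.191 versus 0.326, two-sided 0.05. Remove the claim that 526 per group corresponds to 90.031%, and say that 526 is 219 inflated for dropout and doubled. Add a short table of power over a range of matched fractions and group splits, along the lines of steps 3 and 4 above, labelled as assumptions.

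This costs a paragraph and a small table. Enrolment, data collection and the primary method are unchanged; the one drawback is that a single power figure becomes a range. If the sponsor wishes, overlap weighting from the same propensity model can be added as a further sensitivity analysis at little cost, but this point does not require it.

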### 2.5 Machine learning model

This study proposes a novel multimodal learning model—fused optimized multimodal learning (FOML)—designed to enhance the effectiveness of multimodal data fusion through progressive fusion, orthogonal weighting, and dynamic balancing mechanisms. First, the progressive fusion method retains the advantages of deep fusion while avoiding the feature loss issues associated with traditional early fusion approaches. By gradually integrating information across different layers, this method ensures that shallow-level features guide deeper fusion processes. This approach is expected to perform exceptionally well in future medical image analysis, particularly in scenarios combining imaging and clinical data, where diagnostic accuracy and model generalization capabilities are likely to see significant improvement (11). Secondly, the orthogonal sequential fusion (OSF) strategy sequentially weights and fuses data from each modality, using an adaptive mechanism to reduce inter-modal interference and enhance the unique information extraction capability of each modality. When dealing with data from modalities with significant dimensional differences, such as CT images, MRI scans, and genomic data, the OSF strategy can effectively improve the model's accuracy (12). Finally, the balanced multimodal learning framework addresses the issue of uneven contributions across modalities by dynamically adjusting the learning rate for each modality. In particular, in multi-task learning scenarios, it optimizes the objective function for each modality, enhancing overall task performance and preventing any single modality from exerting excessive influence (13). The method ensures the balanced integration of multimodal data, including images, genomic, and clinical information, in medical image classification tasks, thereby improving diagnostic efficiency and robustness. The FOML model combines three approaches: through the progressive layered fusion, orthogonal weighted fusion, and dynamic balancing mechanisms, not only enhances model accuracy but also strengthens its adaptability to noise and complex data, achieving multi-level integration. Additionally, considering that FOML operates at the task-wise in meta-learning, we implement a three-stage task division: meta-training, meta-validation, and meta-testing. Tasks are grouped and partitioned by domain/subject/scene/institution/time period to ensure mutual exclusivity among the three stages. To mitigate domain transfer overfitting risk, we apply Leave-One-Domain-Out (LODO) cross-validation, sequentially designating each domain as meta-test while using the remaining domains for meta-training and meta-validation, reporting cross-domain averages and variances. All inner-loop updates are constrained by a fixed number of steps and incorporate weight decay and gradient clipping; in cases of class imbalance, task-wise resampling or cost-sensitive loss functions are employed. Final reported metrics and interval estimates (via bootstrap or Bayesian hierarchical models) pertain solely to meta-test tasks, with explicit exclusion of hyperparameter tuning or reuse based on meta-validation tasks.

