The key advantage of the FOML model lies in its ability to handle imbalanced information across modalities. Progressive fusion effectively retains fine-grained information from earlier layers by gradually integrating features, while avoiding the information loss and feature conflicts common in traditional early fusion methods. Orthogonal sequential fusion applies weighted fusion to each modality in sequence, reducing inter-modal interference and preserving the independence and diversity of each modality. Balanced multimodal learning dynamically adjusts learning strategies for each modality, addressing the challenge of uneven contributions and enhancing model performance in complex multi-task learning scenarios. Together, these techniques optimize the model's robustness in the face of data imbalance, noise interference, and high-dimensional feature spaces, making it particularly suitable for high-complexity tasks such as medical imaging and genomics data analysis.

In terms of experimental design, we will validate the FOML model on multiple multimodal medical datasets, encompassing various data types such as image data, gene expression data, and clinical data. To assess the performance of the FOML model compared to traditional fusion methods (e.g., progressive fusion, orthogonal sequential fusion, and balanced multimodal learning) in handling different tasks and data types, we will employ standard statistical analysis methods, including paired *t*-tests, analysis of variance, and Kruskal-Wallis tests, to ensure the statistical significance of performance differences between models. We will pay particular attention to the model's performance in the presence of noise and modality imbalance. We expect the FOML model to demonstrate higher accuracy and robustness under these challenges compared to traditional methods, further validating its superiority and potential applications in multimodal learning tasks.

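### Kruskal-Wallis and one-way ANOVA are the wrong tests for models scored on the same cases; and if domain means hospital, leave-one-domain-out can leave one training hospital per fold

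*Protocol article*

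**What the plan says.** **Model comparison (section 3, Discussion).** The fused model is to be compared with progressive fusion, orthogonal sequential fusion and balanced multimodal learning on several datasets. The tests listed are paired t-tests, then "analysis of variance, and Kruskal-Wallis tests, to ensure the statistical significance of performance differences between models". The article does not say which test serves which comparison, or whether the ANOVA is one-way or repeated-measures.

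**Validation scheme (section 2.5).** There are three stages: meta-training, meta-validation and meta-testing. "Tasks are grouped and partitioned by domain/subject/scene/institution/time period to ensure mutual exclusivity among the three stages". Leave-one-domain-out cross-validation then proceeds by "sequentially designating each domain as meta-test while using the remaining domains for meta-training and meta-validation, reporting cross-domain averages and variances". Interval estimates, by bootstrap or Bayesian hierarchical model, refer to the test tasks only.

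**Sites (section 2.2).** "A total of 1,052 patients with acute large vessel occlusion stroke were enrolled from" three hospitals: "Ya'an People's Hospital, Ganzi Tibetan Autonomous Prefecture People's Hospital, and Liangshan Yi Autonomous Prefecture First People's Hospital". Of the branch sites the article says that "these branch centers primarily served as referral sites or admitted patients who declined endovascular therapy". The sample size per group was doubled to serve the machine learning.

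**The concern.** Two separate matters affect how far the prognostic model's results can be trusted.

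First, when several models predict for the same patients, folds or datasets, their scores rise and fall together, because some cases are harder for every model. A test for independent groups puts that shared variation into its error term, so a real difference between models can be missed almost every time. The plan intends these tests to establish whether the fused model is better.

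Second, the number of folds and the training sample depend on a unit that the article does not fix. Hospital is the natural reading, since institution is on the list and transfer to an unseen site is the usual purpose of this design. With three hospitals and three mutually exclusive stages, one hospital may be all that is left for training. Section 2.2 ties hospital to treatment, so a fold could train mainly on patients without EVT and be tested mainly on patients with it. Much of the benefit of the enlarged sample would then be lost.

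**Working it through.** The article gives no figure for either matter, so there is none to reproduce.

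**A. Unpaired tests on matched scores**

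Inputs: 4 models (the fused model and three named comparators) and two-sided 5% significance (section 2.4). Assumptions: K = 3 or 10 independent folds or datasets; scores with total variance 1 and between-model correlation rho. The article states neither K nor rho.

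Why the one-way test fails: under no difference, the expected between-model mean square is K × (1 − rho)/K = 1 − rho. The expected within-model mean square is rho + (1 − rho) = 1. So F centres near 1 − rho instead of 1; at rho = 0.9 that is 0.1.

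Simulation (2,000 runs; 600 for Kruskal-Wallis). Power is for one model better by one residual SD, √(1 − rho).

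| K | rho | Null rejection: ANOVA | Null rejection: Kruskal-Wallis | Null rejection: paired t | Power: ANOVA | Power: paired t |
|---|---|---|---|---|---|---|
| 3 | 0 | 0.051 | 0.022 | 0.042 | 0.144 | 0.1115 |
| 3 | 0.5 | 0.0145 | 0.003 | 0.0375 | 0.049 | 0.1035 |
| 3 | 0.9 | 0.0015 | 0.000 | 0.054 | 0.006 | 0.1145 |
| 10 | 0 | 0.0495 | 0.062 | 0.049 | 0.561 | 0.503 |
| 10 | 0.5 | 0.0035 | 0.003 | 0.0435 | 0.180 | 0.514 |
| 10 | 0.9 | 0.000 | 0.000 | 0.0465 | 0.0015 | 0.523 |

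The ANOVA is a four-model test and the t-test compares two models. At rho = 0 their power is similar, so the later gap comes from the correlation. Power for Kruskal-Wallis was not simulated; its null rejection falls in the same way. The paired t-test stays near 5% throughout.

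**B. Training hospitals per fold**

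With k domains, one for test and at least one whole domain for validation, at most k − 2 remain for training. For k = 3 that is 1.

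Inputs: 1,052 patients, 526 per group, 20% dropout, and rates of functional independence of 0.191 and 0.326 (all section 2.2). Site sizes are not given, so two cases are shown.

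- *Equal thirds.* 1,052 × 0.8 / 3 = 280.5, about 281 patients. At the average rate (0.191 + 0.326)/2 = 0.2585, about 73 are functionally independent. Pooling two hospitals gives 561 and 145.
- *All EVT patients at one hospital, the rest split equally over two branches.* A branch has 263 × 0.8 = 210.4, about 210 patients, and 210.4 × 0.191 ≈ 40 independent. The EVT hospital has 526 × 0.8 = 420.8, about 421, and 420.8 × 0.326 ≈ 137.

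Without the 20% loss the training folds are 351 (equal thirds), or 263 to 526.

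In the second case, when the EVT hospital is the test domain, whole-hospital stages train on one branch (210). Pooling both branches gives 2 × 210.4 ≈ 421, but still no EVT patients. When a branch is held out, pooling gives 210.4 + 420.8 ≈ 631 with both treatments present.

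**The case against.** **The pairing is not ignored altogether.** Paired t-tests are listed first, and they use it. A reader might infer that every significance claim between models would be invalid. The documents do not support that: the listed paired test holds its level, and under positive correlation the unpaired tests err towards non-significance. The ANOVA might also be meant as repeated-measures. What stands is that Kruskal-Wallis has no matched form under that name, and that the ANOVA is left open.

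**Single-hospital training is not fixed by the text.** The list of partition units also allows subject or time period. The leave-one-domain-out sentence does not say that each stage takes a whole domain. Splitting the two remaining hospitals by patient would satisfy both sentences, and finer domains would leave more for training. This is correct, so the point is conditional. It remains worth settling, because the likeliest reading is the costly one.

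**Two degrees of freedom.** A reader might infer a paired t-test over three hospitals, needing |t| > 4.30. The Discussion ties the tests to several datasets of unstated number, so this cannot be asserted.

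**Gene expression.** The Discussion names datasets "encompassing various data types such as image data, gene expression data, and clinical data". A reader might infer that the study plans to use data it does not collect. The article does not say these data come from this cohort, and a condensed article need not list everything collected.

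**Treatment as an input.** The abstract says the learning was blinded to group. That may mean coded labels, and does not establish that treatment received is excluded.

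**Weight.** The model is to follow the evaluation of EVT and affects no listed outcome, and fold details may sit in the full protocol. This limits the importance of the point. It does not excuse naming an unsuitable test.

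**Conclusion.** The point holds in two parts of different firmness.

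*Firm:* Kruskal-Wallis, and ANOVA if one-way, do not suit scores obtained on the same cases. The cost grows with correlation. With 10 folds, ANOVA power is 0.18 against 0.51 for the paired t-test at rho = 0.5, and 0.0015 against 0.52 at rho = 0.9. The figures assume independent folds and normal scores. That models share cases is not stated outright, but the listing of paired tests presumes it.

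*Conditional:* if domain means hospital and stages take whole hospitals, each fold trains on one site: about 281 patients under equal thirds, or 210 to 421 if EVT is concentrated at one site. Equal thirds and full concentration cannot both hold, since all 526 EVT patients at one hospital would be half the cohort. Because branch sites mainly refer patients or admit those who declined EVT, some folds would train largely on non-EVT patients. It does not follow that the aim of a regional prognostic model must fail.

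The primary comparison of EVT with medical treatment is unaffected.

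**What to change.** 1. **Model comparison.** Replace Kruskal-Wallis and unspecified ANOVA with matched methods. The first choice is a paired patient-level bootstrap of the difference in performance on the same held-out predictions. If the unit is the fold or dataset, use Friedman or repeated-measures ANOVA. With only three folds even the paired t-test had power of about 0.11 in the simulation, which favours the patient-level method.
2. **Domain.** State that the test domain is the hospital and that there are three folds.
3. **Training and tuning.** In each fold, pool the other two hospitals and tune inside them by patient-level resampling, with no separate validation hospital.
4. **Reporting.** Give discrimination and calibration for each held-out hospital, with the bootstrap intervals already planned, and show the number and treatment mix of its training and test patients.

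The cost is wording and analysis code; no extra patients or data are needed. One small downside is that tuning is no longer checked on an unseen hospital, although the final test still is. Pooling also does not fully cure the fold that holds out the main EVT hospital, because the remaining sites may hold few EVT patients. The per-hospital reporting is there so that this fold can be read for what it is.

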**Conclusion:**

This study aims to evaluate the efficacy of endovascular treatment compared with standard medical therapy in patients with LVO-AIS in the Western Sichuan Plateau and to develop an artificial intelligence–based prognostic model to refine treatment strategies for this and other high-altitude regions.

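### Section 2.5 prescribes class rebalancing without a step back to the real outcome rate; if used for predicted probabilities it would overstate independence, and accuracy alone could not show whether the model is useful

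*Protocol article*

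**What the plan says.** The Abstract's conclusion gives the study a second aim besides the treatment comparison: a "prognostic model to refine treatment strategies for this and other high-altitude regions". Section 2.5 describes how that model is trained, in detail that reaches weight decay and gradient clipping. On outcome imbalance it states that "in cases of class imbalance, task-wise resampling or cost-sensitive loss functions are employed". It gives no threshold that triggers the rule, no target class ratio, and no correction of the resulting predictions. It confines final metrics to the meta-test tasks but does not name them.

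The Discussion plans significance tests between fusion methods and says: "We expect the FOML model to demonstrate higher accuracy and robustness under these challenges compared to traditional methods". Accuracy is the only predictive performance measure named in the article. Calibration, AUC and Brier score do not appear.

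The only outcome rates in the article are in Section 2.2, where the control proportion is "assumed to be 0.191 under the null hypothesis and 0.326 under the alternative hypothesis". The article does not say which outcome the model predicts or whether it reports a probability.

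**The concern.** A prognostic model that is meant to inform treatment is most useful when it gives a patient's probability of the outcome. Resampling or cost-weighting trains the model as if the rarer outcome were more common than it is. Unless this is undone, every predicted probability moves towards that outcome. Here the rarer outcome would be functional independence, so the error would be optimistic.

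The one measure named is also poorly suited to judging such a model. When about a quarter of patients have the outcome, a rule that ignores all patient data scores well on accuracy. Rebalancing then moves accuracy in a way that reflects the training ratio as much as the model's merit. The Discussion's comparators are other fusion methods, so one of them could come out best without being shown to beat a simple clinical model or the trivial rule. At stake is the study's second aim.

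**Working it through.** **Inputs.** Section 2.2 gives rates of 0.191 and 0.326, read here as SMT and EVT because their difference is the stated 0.135. It also gives two-sided α of 0.05 (sidedness from Section 2.4), about 90% power, 20% dropout, doubling for machine learning, and 526 per group.

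**The plan's own figure.** The pooled-variance two-proportion formula gives 219 per group. Then 219 × 1.2 = 262.8, rounded up to 263, and 263 × 2 = 526. The figure reproduces, so the two rates are the ones the plan works with.

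**Outcome share.** With equal groups, p = (0.191 + 0.326)/2 = 0.2585. With unequal groups, p lies between 0.191 and 0.326.

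**Shift from rebalancing.** If the model is trained at an outcome share t and not corrected,

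odds shown = odds true × [t/(1 − t)] ÷ [p/(1 − p)], with p/(1 − p) = 0.2585/0.7415 = 0.3486.

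| Training ratio | Odds factor | True 10% shown as | True 25.85% shown as | True 40% shown as |
|---|---|---|---|---|
| 30:70 | 0.4286/0.3486 = 1.23 | 12% | 30% | 45% |
| 40:60 | 0.6667/0.3486 = 1.91 | 18% | 40% | 56% |
| 50:50 | 1/0.3486 = 2.87 | 24% | 50% | 66% |

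Example, last row: 0.1111 × 2.868 = 0.319, and 0.319/1.319 = 24%. At 50:50 the factor is 0.809/0.191 = 4.24 if the share is 19.1%, and 0.674/0.326 = 2.07 if it is 32.6%.

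**Accuracy with no information.** Predicting no independence for everyone is right in 1 − p of patients: 1 − 0.2585 = 74%. The range is 1 − 0.326 = 67% to 1 − 0.191 = 81%.

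**What accuracy shows after rebalancing.** This uses a logistic risk model, logit(risk) = a + b·x, with x standard normal, a set so that the mean risk is 0.2585, and a 0.5 cut-off. The AUC values are assumptions, because the article gives none.

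| AUC | Accuracy, no rebalancing | Accuracy, 50:50 uncorrected | No information | Mean prediction, 50:50 uncorrected |
|---|---|---|---|---|
| 0.64 | 74% | 60% | 74% | 49% |
| 0.74 | 76% | 68% | 74% | 46% |
| 0.82 | 80% | 74% | 74% | 43% |
| 0.87 | 83% | 78% | 74% | 40% |

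The true mean is 26% in every row. At AUC 0.74 the Brier score goes from 0.163 without rebalancing to 0.206 with uncorrected 50:50 rebalancing. Predicting 25.85% for everyone scores 0.2585 × 0.7415 = 0.192, so the rebalanced model's probabilities are worse than that constant, although it ranks patients exactly as well as before. Dividing the predicted odds by 2.87 undoes the shift in this setting and returns the mean to 25.85%.

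**The case against.** The strongest reply is that several stronger readings go beyond the text, and that reply is right on these points:

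- **That the model will be judged on accuracy.** A reader might infer this, but Section 2.5 leaves the final metrics unnamed and the Discussion states an expectation, not a metric.
- **That the plan decides against recalibration.** The article is a condensed account and a fuller analysis plan may exist. Silence is not a decision.
- **That predictions will be far too high.** Rebalancing is conditional, its ratio is open, and a split of about 26:74 is moderate, so the rule may not be triggered. The 2.87-fold factor needs full 1:1 balancing. At 30:70 the overstatement is about four percentage points for a patient at the pooled rate.
- **That accuracy cannot register the shift.** At a 0.5 cut-off it does: at AUC 0.74 it falls from about 76% to about 68%, below the 74% of the trivial rule.
- **That functional independence is the target and probabilities are the output.** Neither is stated. If only rankings or class labels are used, the argument about shifted probabilities does not apply.

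It could also be said that choosing metrics is routine analysis-plan content. That holds for a bare omission. Here, however, the article itself states a training rule that distorts probabilities, at a level of detail where the matching correction would belong. The only performance property set beside that rule does not separate a well-ranking but miscalibrated model from an uninformative one: at AUC 0.82, uncorrected 1:1 rebalancing gives the same 74% as the trivial rule.

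**Conclusion.** The point holds in conditional form. If rebalancing is used, if the target is 90-day mRS 0–2 and if probabilities are reported, the rule as written overstates the chance of independence. The direction is certain under those conditions; the size depends on the unstated ratio. At a pooled rate of 25.85% with equal groups, a patient at that rate is shown 30% to 50% across 30:70 to 50:50.

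Whatever the training ratio, for that target accuracy of up to about 74% (67% to 81% across the two assumed rates) demonstrates nothing beyond a trivial rule, so accuracy alone cannot show whether the model is useful. The documents do not support the claim that clinicians will be given badly inflated figures, or that the study has chosen accuracy as its criterion. The weakness is confined to the prediction-model aim and is cheap to repair, so it should be dealt with.

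**What to change.** In Section 2.5, name the outcome predicted and say whether probabilities are reported. Then choose one of two routes: train without resampling or cost-weighting, or keep the rule and recalibrate predictions to the un-resampled outcome rate using data outside the meta-test set.

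On the untouched meta-test patients, report calibration intercept and slope, Brier score and AUC as the main measures. Set them beside a clinical logistic model and the no-information accuracy, and keep accuracy as descriptive only.

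The cost is a few lines of wording, one recalibration step in code and a few extra metrics, with no new patients or data. Reported performance may look less favourable than a single accuracy figure would. The EVT versus SMT analysis in Section 2.4 needs no change.
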